### Plans for collection, laboratory evaluation, and storage of biological specimens for genetic or molecular analysis in this trial/future use {33}

Not applicable, no biological specimens collected.

## Statistical methods

### Statistical methods for primary and secondary outcomes {20a}

To test the effect of the intervention on women with and without disability, analyses will be initially conducted separately for each group. To determine whether the interventions have any specific effect on women with disability, in comparison to those without disability, data for women with and without disability will be analysed together with an interaction term between intervention status (yes or no) and disability status (yes or no).

The primary outcome will be modeled as access to family planning as defined in Table 2, the proportion for which will be reported for each arm. As the primary and secondary outcomes are based on dichotomous measures with grouping of respondent outcomes within health facility catchment areas, multilevel logistic regression will be used to investigate the association between disability status with the outcomes of interest. Basic respondent and health facility catchment area characteristics will be used in the regression, in addition to random-effects at the cluster level. Any other variables that appear to be imbalanced at baseline will be included in an adjusted analysis that will be reported separately.

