### Objectives {7}

Informed by the population, intervention, control and outcome (PICO) defined in Table 1, the cluster randomized controlled trial aims to answer the following research questions:Did the intervention increase access to family planning amongst women with disabilities in selected sites in Kaduna city?Did the intervention increase use of family-planning services amongst women with disabilities in selected sites in Kaduna city?Did the intervention reduce the unmet need for family-planning services amongst women with disabilities in selected sites in Kaduna city?

**Table 1 Tab1:** PICO for cluster-randomized controlled trial of the IFPLAN project

Population	Women aged 18^a^–49 years that report at least ‘a lot’ of difficulty on one of the six questions in the Washington Group short set or ‘daily’ and ‘a lot’ to additional questions on depression or anxiety; women in the same neighbourhood and age range without disabilities, in order to determine whether the intervention has a specific effect amongst women with disabilities
Intervention	Components of the IFPLAN project delivered at the health facility and community levels, in the context of state-wide and national broadcast media and advocacy
Control	‘Standard’ provision of family planning services in the state, in the context of state-wide and national broadcast media and advocacy
Outcome	Primary: Access to family planning Secondary: Knowledge, unmet need, and use of family planning

^a^The evaluation will include women aged 18–49 years, as opposed to the target age of 15–49 years in the IFPLAN project, as it was considered not acceptable to interview women under 18 years regarding their sexual and family planning practices, given the sensitive nature of the research topic and the need for caregiver consent for minors to participate

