### Methods in analysis to handle protocol non-adherence and any statistical methods to handle missing data {20c}

We will adopt an intention-to-treat analysis, and therefore health facility catchment areas will be analysed per their original arm assignment even if subsequently the intervention is not implemented in any or all of the health facilities in that cluster. Given that the health facility catchment areas are close together due to the small geographical area of Kaduna city, respondents will be asked about which facility they attend for family planning services and their participation in community-based family-planning activities in order to conduct a sensitivity analysis using an as-treated per-protocol analysis. Furthermore, should health facility staff be transferred between facilities from the intervention arm to control arm (or vice versa) this will be captured through the process evaluation and its potential effects explored.

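### The only sentence naming the regression model gives disability status, not allocated arm, as the exposure, contradicting the section's own aim of testing the intervention effect

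*Protocol article*

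**What the plan says.** Everything here is in the protocol article; no separate analysis plan is shown.

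- **Objectives {7}.** The first research question is "Did the intervention increase access to family planning amongst women with disabilities in selected sites in Kaduna city". The other two ask the same about use and unmet need.
- **Statistical methods {20a}, first paragraph.** The aim and the analysis sets are given as "To test the effect of the intervention on women with and without disability, analyses will be initially conducted separately for each group". A pooled analysis follows, with an interaction between intervention status and disability status.
- **Statistical methods {20a}, second paragraph.** For the primary outcome, access to family planning, "the proportion for which will be reported for each arm". The model is then named: "multilevel logistic regression will be used to investigate the association between disability status with the outcomes of interest". The other terms are described as "Basic respondent and health facility catchment area characteristics will be used in the regression, in addition to random-effects at the cluster level".
- **Sample size {14}.** The calculation is for a risk ratio of 1.5 in access against the control arm, with 25 women with disabilities per cluster.
- **Non-adherence and missing data {20c}.** Under intention to treat, "health facility catchment areas will be analysed per their original arm assignment".
- **Additional analyses {20b}.** The subgroup of women with functional difficulty is to be analysed by the same approach as the primary and secondary indicators.

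**The concern.** A randomised trial's main model should have allocated arm as its exposure. Here the sentence that names the model gives disability status that place, and the sentence listing the other terms does not name arm either. Disability status is a characteristic of the respondent and was not randomised. Its coefficient answers whether women with disabilities differ from their neighbours, not whether the intervention worked.

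At stake is whether the primary comparison is fixed in advance. The section on blinding {17a} states that the data analyst will not be blinded. The exposure of the main model should therefore be unambiguous before endline outcomes are analysed. If an analysis plan or analysis code copied the sentence as it stands, the error would carry forward. It would also pass to the functional-difficulty subgroup, where every woman has a disability by definition.

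**Working it through.** **1. Which contrast was the trial sized for?** Inputs from Sample size {14} and Table 4: p0 = 0.25, risk ratio 1.5 so p1 = 0.375, m = 25 per cluster, k = 0.3, 5% significance (two-sided assumed, since sidedness is not stated), 80% power. The Hayes and Bennett formula for unmatched clusters is

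c = 1 + (z₀.₉₇₅ + z₀.₈₀)² × [p0(1−p0)/m + p1(1−p1)/m + k²(p0² + p1²)] / (p1 − p0)²

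- p0(1−p0)/m = 0.1875/25 = 0.0075
- p1(1−p1)/m = 0.234375/25 = 0.009375
- k²(p0² + p1²) = 0.09 × (0.0625 + 0.140625) = 0.01828
- Sum = 0.03516; divided by 0.125² = 0.015625, this is 2.25
- (1.960 + 0.842)² = 7.849; 7.849 × 2.25 = 17.66; c = 18.66, rounded up to 19

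19 × 25 = 475 per arm and 2 × 475 = 950, which matches the abstract. The stated size is therefore for intervention versus control among women with disabilities.

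**2. Can the named model be fitted in the separate analyses?** Among women with disabilities the disability indicator equals 1 for everyone, so it duplicates the intercept. A design matrix of intercept plus disability status has two columns and rank 1. The coefficient is not estimable. The same holds among women without disabilities, where the indicator is always 0.

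**3. What does it estimate in pooled data?** The model outcome ~ disability returns a contrast between disability groups and no arm term. This was illustrated with one simulated data set: 37 clusters (19 and 18), 25 women of each disability status per cluster, access of 25% in control and 37.5% in intervention before cluster variation, and no true difference by disability. Logistic GEE clustered on catchment area stood in for the multilevel model. The true log odds ratio for arm is ln[(0.375/0.625)/(0.25/0.75)] = ln 1.8 = 0.588.

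| Model | Data | Estimates (log odds scale, SE) |
|---|---|---|
| outcome ~ disability | pooled | disability 0.127 (0.102); no arm coefficient |
| outcome ~ arm | with disabilities | arm 0.596 (0.171) |
| outcome ~ arm | without disabilities | arm 0.569 (0.203) |
| outcome ~ arm × disability | pooled | arm 0.569 (0.203); disability 0.114 (0.165); interaction 0.027 (0.212) |

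In the last row the arm effect in women with disabilities is 0.569 + 0.027 = 0.596, as in the separate model. Models with arm recover the intervention effect; the model as worded does not contain it.

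**4. The statements side by side.** The research questions, the opening aim of {20a}, the interaction analysis, the proportions by arm, the sample size and the intention-to-treat rule all concern the allocated arm. The sentence naming the regression is the only one that makes disability status the exposure.

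**The case against.** The strongest reply is that this is a slip in wording whose meaning is clear from its surroundings. {20a} opens by stating that the intervention effect is to be tested in each group. It commits to proportions by arm. Before the sentence at issue, it sets out a pooled interaction model which, fitted with its main effects as is usual, yields the arm effect in women with disabilities. Because the literal model cannot be run in the separate sets, an analyst would notice and use arm. All of this stands, and it limits the point.

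It does not remove it. A stated aim and descriptive proportions do not specify a model, and the interaction term answers a different question: whether the effect differs by disability. Nor is this a detail left to an analysis plan, since the article does name an exposure and names the wrong one. Arm might be counted among the catchment-area characteristics, but it would then be an adjustment variable rather than the exposure.

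Two stronger readings are tempting, and the document supports neither:

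- A reader might infer that the trial, run as planned, would give no estimate of the intervention effect. That follows only if the one sentence is read apart from the rest of {20a} and {20c}.
- A reader might put a size on the disability contrast from the met-need figures in the Background, 19% with and 28% without disabilities: (0.19/0.81)/(0.28/0.72) = 0.60. This illustrates only that such gaps can exist. Met need is not the primary outcome. The survey behind those figures did not count psychosocial disability, whereas in Table 4 depression or anxiety supplies 6.0 of the 6.49 percentage points of assumed disability prevalence. The trial's comparison women are also matched on neighbourhood and age. The size, or even the presence, of a gap in the primary outcome is not given.

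**Conclusion.** The exposure of the primary model is stated wrongly and contradicts the section's own aim, the objectives, the sample size and the intention-to-treat rule. As worded, the model cannot be estimated in either separate analysis, and in pooled data it estimates a non-randomised contrast. The intended comparison of arms is recoverable, so this is a misstatement to correct before endline analysis, not evidence that the trial lacks an intervention-effect analysis.

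The size is one term in one sentence, but in the model for the primary and secondary outcomes. No design or power figure moves, because 950 women is already an arm-versus-arm number. The contradiction and the non-estimability rest on the text and on algebra. The simulation is a single illustrative draw. A separate analysis plan, if there is one, may already name arm; the article's sentence would still need correcting to agree with it.

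**What to change.** Replace the sentence that names the regression with wording such as:

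*A multilevel logistic model with a random effect for cluster will estimate the association between allocated arm and each binary outcome. It will be fitted first in women with disabilities, which is the primary comparison, and then in women without disabilities. A pooled model will contain allocated arm, disability status and their interaction.*

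The existing sentences on covariates and on the separately reported adjusted analysis can stay. Covariate coding can be left to the analysis plan. The functional-difficulty subgroup then inherits a model that can be fitted.

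The cost is one sentence, with no effect on data collection, sample size or fieldwork. The change should be dated and recorded through the route the article gives for protocol modifications, ideally before endline outcomes are analysed.

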### Sample size {14}

Calculations were conducted in Microsoft Excel [31], based on Hayes & Bennett [32]. The assumptions, as summarized in Table 4, were used in determining the likely number of women 18–49 years with disabilities who will be living in the catchment areas of the healthcare facilities, as this is the target population for the evaluation. Various plausible estimates of the between-cluster coefficient of variation (*k*) and effect sizes were explored. Determination of the sample size was guided by the number of areas that the Sightsavers team has capacity and funding to reach, and security concerns limiting implementation to Kaduna city. Assuming *k* = 0.3, a 5% significance level, and 80% power, the trial will be able to detect a risk ratio of 1.5 (i.e. a 50% increase in access compared to the control arm) with 25 women with disabilities interviewed in each cluster. This design will require approximately 20,000 households to be screened for eligible women. It was originally intended to have 19 clusters per arm (a total of 38 clusters overall); however, it was only possible to identify a total of 37 clusters in Kaduna city, consequently 19 clusters were assigned to the intervention arm and 18 clusters to the control arm.

**Table 4 Tab4:** Assumed and derived values for the IFPLAN cluster randomized controlled trial sample size calculations

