**Assumptions:**	
Proportion of women aged 18–49 years	20.0%
Proportion of women 18–49 years who are disabled based on Washington Group Questions^a^	0.7%
Proportion of women 18–49 years with depression or anxiety^b^	6.0%
Estimated overlap between the above	30%
Number of people in each cluster	10,000
Proportion of women who have ‘access’ to family planning	25%

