## Assignment of interventions: allocation

### Sequence generation {16a}

Cluster allocation was conducted through a random draw. The first 19 clusters drawn were allocated to the intervention arm and the remaining 18 clusters allocated to the control arm.

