## Data collection and management

### Plans for assessment and collection of outcomes {18a}

Data will be collected by experienced and trained female enumerators, overseen by OPM Nigeria. All data collection tools and procedures will be pre-tested and piloted prior to use.

The trial will collect baseline and endline data from all of the health facility catchment areas included in the study using household surveys. The baseline survey will be conducted prior to implementation of the project interventions and the endline survey will be conducted after at least 1 year of IFPLAN activity implementation.

Project monitoring data will be routinely collected by implementing partners to support intervention implementation and shared with LSHTM for the purposes of the process evaluation. During and/or after the IFPLAN project, semi-structured interviews will be undertaken with women of reproductive age with disabilities in the intervention arm to understand participant responses to the interventions, identify any unintended consequences, and compare their experiences to women without disabilities in the intervention arm, and women with disabilities in the control arm (approximately 30 interviews conducted in total). Furthermore, key health facility staff and intervention implementers will be interviewed to elucidate mechanisms of impact and contextual factors for implementation.

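### Cluster-level baseline access is collected but not named as a covariate, and covariates beyond an unlisted basic set enter only if they appear imbalanced

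*Protocol article*

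**What the plan says.** Item 18a states: "The trial will collect baseline and endline data from all of the health facility catchment areas included in the study". Table 3 shows the same survey modules at both rounds, including knowledge of contraceptive methods and contraceptive use.

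Item 20a specifies a multilevel logistic regression with cluster random effects. Basic respondent and catchment-area characteristics are always included, but they are not listed. The next sentence governs everything else: "Any other variables that appear to be imbalanced at baseline will be included in an adjusted analysis that will be reported separately". Baseline access is not named.

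Item 21b gives the baseline data two uses: checking balance between arms and informing project indicators. The balance factors it mentions are socio-economic ones and those likely to affect implementation. The baseline level of the outcome is not named there either.

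On allocation, item 16a says: "Cluster allocation was conducted through a random draw". No stratification or restriction is described. Item 17a says that the data analyst is not blinded.

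**The concern.** In a cluster trial, the cluster's own starting level of the outcome is a natural candidate for adjustment. Here it will already be in the data. Two things follow from how the plan is written.

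First, unless baseline access is among the unlisted basic characteristics, it falls under the imbalance rule. That rule lets in a covariate because the arms happened to differ on it, not because it predicts the outcome. A prognostic covariate improves precision even when the arms are balanced, and the rule gives that up.

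Second, the rule has no criterion for when a variable appears imbalanced, and the analyst who applies it knows the allocation. It also yields two reported analyses without saying which prevails if they disagree.

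At stake are precision and protection in the event of a chance imbalance in starting access. A simple draw of 37 clusters does nothing to prevent such an imbalance. Validity of the test over all possible allocations is not at stake.

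**Working it through.** **Inputs from the protocol (item 14, Table 4).** "Assuming *k* = 0.3"; "a 5% significance level, and 80% power" (two-sided assumed); control proportion p0 = 0.25; risk ratio 1.5, so p1 = 0.375; m = 25 women per cluster; 18 control and 19 intervention clusters.

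**Assumed, not in the documents.** The cluster autocorrelation (CAC), meaning the correlation between a cluster's true access at baseline and at endline, is taken over 0 to 1. Different women are assumed to be interviewed at endline. Table 3 repeats the household listing, but the protocol does not say whether the same women are re-interviewed.

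**1. The plan's own figure.** Variance of a cluster proportion = p(1−p)/m + k²p².
- Control: 0.0075 + 0.005625 = 0.013125.
- Intervention: 0.009375 + 0.012656 = 0.022031.
- Sum: 0.0352, of which 0.0183 (52%) is between clusters.
- Clusters per arm = 1 + (1.96 + 0.84)² × 0.0352 / 0.125² = 18.66 with unrounded normal quantiles. This rounds up to 19, and 19 × 25 × 2 = 950. The stated design reproduces.

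**2. Power without covariates at 18 and 19 clusters.** Standard error = √(0.013125/18 + 0.022031/19) = 0.0435. Noncentrality = 0.125/0.0435 = 2.88. A noncentral t with 35 df gives 79.9%.

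**3. Power with cluster baseline access as covariate.** Reliability of a baseline cluster proportion = 0.005625/0.013125 = 0.43. The correlation of observed proportions is r = CAC × 0.43, and the variance is multiplied by 1 − r². Power uses 34 df.

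| CAC (assumed) | Variance factor | Power |
|---|---|---|
| 0 | 1.000 | 79.8% |
| 0.2 | 0.993 | 80.1% |
| 0.3 | 0.983 | 80.4% |
| 0.5 | 0.954 | 81.6% |
| 0.8 | 0.882 | 84.5% |
| 1.0 | 0.816 | 87.1% |

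This applies the control-arm reliability to both arms. Arm-specific correlations give 82.1 / 85.6 / 88.7% at CAC 0.5 / 0.8 / 1.0. A simulated cluster-level ANCOVA (20,000 runs per scenario) gives 79.7 / 81.5 / 84.3 / 88.2% at CAC 0 / 0.5 / 0.8 / 1.0, against 80 to 81% unadjusted. At CAC 0 the simulated loss is about 1 point, because the slope must be estimated; the formula shows 0.1 point.

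**4. Chance imbalance.** SD of the between-arm difference in true baseline access = √(0.005625 × (1/18 + 1/19)) = 0.0247. That is 2.5 percentage points (95% range about ±4.8), against a target difference of 12.5.

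**5. The imbalance rule.** The simulation read the rule as adjusting only when baseline access differs at p < 0.05, with CAC 0.8. It triggered in about 5% of trials and left power at 80%, against 84% with pre-specified adjustment. With no true effect, and among the triggered trials only (about 920 of 20,000), the unadjusted test rejected about 10% of the time and the adjusted test about 5%. Over all trials every approach stayed near 5% (4.5 to 5.3% across the CAC values tried).

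**The case against.** Several stronger readings are tempting, and the documents do not support them.

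- *A reader might infer that covariates enter only if imbalanced.* Item 20a contradicts this: the basic characteristics enter regardless, and the rule governs only the remaining variables, in a separate analysis.
- *A reader might infer that baseline access is definitely excluded.* The basic catchment characteristics are not listed. A cluster's baseline proportion could be among them, and an analysis plan that is not shown may say so. The text supports only that it is not named.
- *A reader might call the power gain free.* It depends on a correlation the documents do not give, and with 25 women per cluster the baseline proportion is a noisy measure.
- *A reader might infer an inflated false-positive rate.* Overall it is not inflated. A chance difference in starting access is ordinary randomization variation, already reflected in the standard error.

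The comparator also matters. The 79.9% credits the plan's basic covariates with nothing. If they explained 30% or 50% of the between-cluster variance (assumed), adding baseline access at CAC 0.8 would gain about 2.5 or 1.3 points. At CAC 0.5 it would gain about 0.9 or 0.5.

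Finally, item 21b places the balance check on baseline data, and the imbalance rule is broad enough to bring baseline access into the separate analysis.

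All of this limits the size of the point. What remains is a published rule that selects covariates by observed imbalance with no stated criterion. An analysis plan would have to reverse that rule, not merely fill it in. The Discussion's remark that a woman's baseline position is no guide to her endline position concerns individual desires. It does not rule out a cluster-level covariate.

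**Conclusion.** The point holds as a recommendation about method and does not make the primary analysis invalid. Pre-specified adjustment for cluster baseline access is better than the stated rule. Relative to a comparison without covariates, the change in power runs from roughly nil, or a loss of up to about 1 point, at zero correlation, through about 2 points at CAC 0.5 and 5 at 0.8, to about 7 at 1.0. It is smaller to the extent that the basic covariates already explain cluster differences.

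These figures rest on the plan's k, p0 and m, on an assumed CAC, on new women at endline, and on a cluster-level approximation to the multilevel logistic model. If the same women were followed, the gain could be larger: about 91% power at an assumed individual correlation of 0.3 and cluster correlation of 0.8. With planned power at 79.9%, a few points are worth having, but they cannot be promised.

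**What to change.** Before the endline data are examined:

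1. Pre-specify the cluster's baseline proportion with the outcome as a covariate in the primary model for each binary outcome. For the primary analysis, compute it among women with disabilities.
2. List the basic respondent and catchment-area characteristics, and fix any others now by expected prognostic value.
3. Delete the imbalance-triggered rule. Baseline balance can still be described, but it should not select covariates.

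The cost is a change of wording in the analysis plan and one degree of freedom out of 35. If baseline and endline cluster access prove uncorrelated, the power lost is small (0.1 point by formula, about 1 point in simulation). No new data are needed.
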